##### **6.1.2.1 Sample Size Considerations**

According to Initiative on Methods, Measurement, and Pain Assessment in Clinical Trials (IMMPACT) recommendations, pain intensity reductions of 30% to 50% or more are considered useful. Therefore, the estimated sample size was calculated based on a reduction of 50% in the HBOT group and a reduction of 20% in the medication group, with a standard deviation of 40% [65, 66]. Assuming a power of 80%, and 5% two-sided level of significance, a total of 58 participants would be required, 29 participants in each arm. Considering a dropout rate of 15% the total sample size required is 70.

|                                                     |                                                        |                                        |
|-----------------------------------------------------|--------------------------------------------------------|----------------------------------------|
| Investigational Product
Hyperbaric chamber       | Short Title:                                           | Protocol No.
058-17-ASF             |
| Phase:
Investigator Initiated Phase
III study | Hyperbaric Oxygen Therapy for Fibromyalgia
Syndrome | Version, Date
Ver.4.0, 10 OCT, 2017 |

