### 3.2.1 HBOT protocol

A total of 60 daily hyperbaric oxygen treatment sessions will be administrated 5 days per week. Each session will include exposure of 90 minutes to 100% at 2 ATA, with 5 minutes air breaks every 20 minutes.

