### 3.2.2 Pharmaceutical protocol

Patients will be offered pharmacological treatment with one of the two medications currently licensed for the treatment of FMS in Israel, i.e. Cymbalta and Lyrica. Treatment with Lyrica will start at a dose of 75 mg at bedtime while treatment with Cymbalta will start at a dose of 30 mg a day (in the morning). After a period of 6 weeks patients will be evaluated and dose will be adjusted as necessary. Patients may also be switched from one medication to the other based according to clinical judgment.

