### 3.2.3 Crossover

After 3 months of either pharmaceutical or HBOT, once the 2nd evaluation is completed, all patients in both groups will be offered to switch to the alternative treatment group.

|                                                     |                                                        |                                        |
|-----------------------------------------------------|--------------------------------------------------------|----------------------------------------|
| Investigational Product
Hyperbaric chamber       | Short Title:                                           | Protocol No.
058-17-ASF             |
| Phase:
Investigator Initiated Phase
III study | Hyperbaric Oxygen Therapy for Fibromyalgia
Syndrome | Version, Date
Ver.4.0, 10 OCT, 2017 |

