## 4. Study endpoints

### 4.1 Primary endpoint

The primary end point of the study will be the measurement of daily pain on a (0-10) Visual analogue Scale (VAS) [42]

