#### *6.1.2 Primary Efficacy Analysis Set*

The primary endpoint parameter: *improvement in fibromyalgia questionnaires scores* will be measured following the 1st treatment period and separately after the crossed treatment period.

The primary efficacy analysis evaluation will include all subjects who completed the treatment period, had no major protocol violations.

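### No pain rating common to both arms is scheduled between baseline and month 3, and the completer-only primary set excludes the planned 15% dropouts, for whom no post-baseline outcome is assured

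*Protocol*

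**What the plan says.** - **Endpoint (Protocol 4.1):** "The primary end point of the study will be the measurement of daily pain on a (0-10) Visual analogue Scale (VAS"). No recording frequency, averaging window or visit is given.
- **Timing (Protocol 6.1.2):** the primary parameter is measured after the first "treatment period and separately after the crossed treatment period". This section names questionnaire scores as that parameter, whereas 4.1 and the sample-size section use pain. I take the timing to apply to the primary outcome, whichever it is.
- **Visits (Protocol 3.2.3):** the switch is offered "After 3 months of either pharmaceutical or HBOT, once the 2nd evaluation is completed". If the month-3 evaluation is the second and baseline the first, no study evaluation lies between them.
- **Week 6, medication arm (Protocol 3.2.2):** "After a period of 6 weeks patients will be evaluated and dose will be adjusted as necessary". No pain score is named, and the HBOT section has no counterpart.
- **HBOT attendance (Protocol 3.2.1):** "A total of 60 daily hyperbaric oxygen treatment sessions will be administrated 5 days per week".
- **Analysis set (Protocol 6.1.2):** "The primary efficacy analysis evaluation will include all subjects who completed the treatment period, had no major protocol violations".
- **Dropout (Protocol 6.1.2.1):** "Considering a dropout rate of 15% the total sample size required is 70". Dropout is not defined. Nothing says whether a participant who stops treatment is still assessed at month 3.

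**The concern.** The plan expects about one participant in seven to leave, removes leavers from the primary analysis, and expressly schedules no earlier outcome on a scale shared by both arms. Reasons for leaving a 60-session chamber course may well differ from reasons for leaving an offered, switchable drug. If leavers fare worse than stayers by different amounts in the two arms, the completer comparison is biased. Without an assured interim rating there may be nothing from which to see or correct this.

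An SAP can choose a missing-data method, but it cannot supply ratings that were never taken. The schedule therefore has to be settled in the protocol. The omission is avoidable, because both arms are already in contact at about week 6.

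**Working it through.** **1. The plan's own sample size.** Inputs from 6.1.2.1: "a reduction of 50% in the HBOT group and a reduction of 20% in the medication group", SD 40%, power 80%, two-sided 5%.
- Normal approximation: 2 × (1.96 + 0.84)² × 40² / 30² = 27.9, so 28 per arm.
- Noncentral t: 28 per arm gives 78.7% power and 29 gives 80.1%. The stated 29 per arm (58 in total) reproduces.
- Dropout: 29 / 0.85 = 34.1, so 35 per arm and 70 in total. This also reproduces.

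**2. Planned leavers.** 0.15 × 70 = 10.5, so 10 or 11. That leaves 59 or 60 completers against the 58 required.

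**3. Contact at week 6.** HBOT: 60 sessions / 5 per week = 12 weeks, so week 6 is mid-course and participants are on site. The medication arm has its 6-week evaluation.

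**4. Possible bias of the completer difference.** Assume 15% dropout in each arm, and completers at the planned 50% and 20% reductions. The protocol gives only an overall dropout rate and no leaver outcomes, so the leaver columns below are assumptions. The all-randomised difference is

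(0.85 × 50 + 0.15 × L_H) − (0.85 × 20 + 0.15 × L_D),

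where L_H and L_D are the mean reductions of HBOT and medication leavers. Bias is 30 minus this.

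| L_H | L_D | HBOT mean | Medication mean | Difference | Bias |
|---|---|---|---|---|---|
| 20% | −10% | 45.5 | 15.5 | 30.0 | 0 |
| 20% | 0% | 45.5 | 17.0 | 28.5 | 1.5 |
| 20% | 20% | 45.5 | 20.0 | 25.5 | 4.5 |
| 0% | 0% | 42.5 | 17.0 | 25.5 | 4.5 |
| 0% | 20% | 42.5 | 20.0 | 22.5 | 7.5 |

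Equivalently, bias = 0.15 × [(50 − L_H) − (20 − L_D)]. It is zero when leavers fall short of stayers by the same amount in both arms, and it changes sign when the shortfall is larger in the medication arm.

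**5. Information a week-6 rating could recover.** Assume half of the leavers go after week 6 (10.5 / 2 = 5.25), and that week-6 and month-3 ratings correlate 0.6 to 0.8. As an approximation, each such leaver contributes about the squared correlation of one completer.
- 5.25 × 0.36 = 1.9 and 5.25 × 0.64 = 3.4 patient equivalents.
- Against 59.5 completers, that is 1.9 / 59.5 = 3% to 3.4 / 59.5 = 6% more information.
- The standard error falls by 1 − √(59.5 / 61.4) = 1.6% to 1 − √(59.5 / 62.9) = 2.7%.

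**The case against.** **A reader might infer that dropouts have no post-baseline outcome at all.** The protocol does not establish that. Daily pain may mean a daily rating, in which case interim data would exist. The content of the medication arm's week-6 evaluation is unstated. A participant who stops treatment might still attend at month 3. This objection stands: the supportable statement is that no such outcome is assured. It does not remove the point, because the text leaves the recording schedule open.

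**A reader might also infer that the figure of 70 is wrong.** It is not. Both the 58 and the allowance for dropout reproduce, and nothing here changes a sample-size input.

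**Missing data belong to the SAP, which is not shown.** This stands for the choice of method. It does not stand for data collection, or for the completer rule, which the protocol itself fixes.

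**A week-6 rating alone would change nothing.** This is correct. The completer rule in 6.1.2 would keep leavers out of the primary analysis however many ratings they gave, so the schedule and the analysis set have to change together.

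**The gain is small.** This also stands. Participants who leave before week 6 contribute no week-6 rating. In the medication arm, dose changes at week 6 and permitted switching may weaken the correlation with month 3. Any bias correction also requires that dropout be explained by the ratings observed.

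**Conclusion.** The point holds in a limited form. The protocol expressly schedules no pain rating common to both arms between baseline and month 3, and it confines the primary analysis to completers. The 10 to 11 planned dropouts are therefore excluded, with no post-baseline outcome assured.

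The size of any bias is not established. It runs from 0 to about 7.5 of the planned 30 points over the leaver outcomes tried, given 15% dropout in each arm. It would be tempting to quote 4.5 points as the expected bias, but one route to that value requires HBOT leavers to do worse than stayers while medication leavers do as well as stayers, and the documents support no single scenario.

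The information recoverable from a week-6 rating is about 2 to 3 patient equivalents under the assumed timing and correlations, and less if week-6 dose changes weaken the correlation. This is a worthwhile, inexpensive improvement and not a defect that undermines the trial.

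**What to change.** 1. In Protocol 4.1, state when and how often the 0–10 pain VAS is recorded, identically in both arms, and include a rating at week 6.
2. Define dropout, and state that the month-3 VAS will be sought from participants who stop treatment.
3. In Protocol 6.1.2, replace the completer-only primary set with all randomised participants who have data. Analyse baseline, week 6 and month 3 in one repeated-measures model, with the month-3 difference between arms as the primary contrast. A completer analysis can remain as supportive.

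The cost is one extra self-rating per patient at contacts that already exist, plus revised wording of the schedule and analysis set in the protocol and matching text in the SAP. No treatment or visit changes, and the sample size stays at 70.
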